**Fig. 2 Fig2:**
[figure not shown]
Phase 2 flow chart: This diagram illustrates a study flow chart adapted from the CONSORT and includes a blank template of what will be reported

### Blinding (phase 2 only)

The principal investigator and biostatistician will remain blinded until the completion of data collection (i.e., data is locked). Following the conclusion of data collection (i.e., data is locked), the biostatistician will be unblinded as data analysis will require knowledge of treatment assignment. The study coordinator and graduate student worker that deliver the intervention(s) and prepare reports to the Independent Monitoring Committee (IMC) will be unblinded. The study coordinator will be responsible for the intervention groups, and the graduate student worker will be responsible for the control group. A research staff not directly involved in the study will serve as the “trusted broker” to handle the sequential assignment of participants to randomized treatment groups and will also be unblinded.

### Incentives

Phase 1 and 2 incentives are listed in Table 4.

**Table 4 Tab4:** Incentive schedule

Phase	Time point	Incentive
Phase 1—iterative design	Completion of review of 9 yoga videos	•Free 1 month membership to UDAYA •$15/session (up to $135 gift card)^b^
Phase 1—interviews	Completion of 15-min interview	$15 gift card^b^
Phase 2	Enrollment	•Intervention groups: yoga mat, 2 blocks, and strap •Control group: stretching mat and band •12-week membership to UDAYA^a^
	Baseline	Survey: $10
	Post-intervention	Survey: $10 Interview: $15
	Follow-up	Survey: $25 Interview: $10

^a^All groups receive incentive

^b^Participant has choice of gift card from Amazon, Bath & Body Works, Starbucks, or Target

### Data management

The research participant will self-report data electronically via Qualtrics. Weekly, the research team will be responsible for ensuring the completeness and timeliness of the data reported by the participants. Additionally, the research team will skim the data after each collection time point to ensure it is complete and will follow-up with any participants in which data collection is not complete.

Data quality will be monitored throughout the study. Measurement values will be compared to their known ranges. Out of range values will be investigated and either corrected if possible or treated as missing data. Statistical analyses will adjust for baseline demographic characteristics when statistically appropriate. Multiple imputations will be used to conduct statistical analysis with missing data. In the event that the missing at random assumption is violated, we will model the missing data mechanism and conduct sensitivity analysis on model parameters.

We have multiple strategies in place to identify yoga participation both during video sessions and outside of video sessions. First, we will be collecting 24-h, time-stamped GENEActiv accelerometer data at baseline, post-intervention (12 weeks), and follow-up (20 weeks) and will have a full record of their activity level during these time points. We will also be monitoring UDAYA website log-in information and will be able to localize activity monitor data while the participant is logged into the website and using the yoga videos. This will allow us to verify whether the participant is being active during the times they are using the website. Second, we will collect self-reported minutes of yoga using a log. This self-report log will also give us a time stamp of yoga activity that we will be able to cross-refer to the accelerometer data. Finally, we will be able to monitor all other physical activities that are performed outside of yoga, examining whether the intervention may have unintended effects of activity within other types of physical activity. Collectively, we will have a full record of yoga and physical activity (outside of yoga) participation that we will be able to use to understand the “dosage” that is being achieved for this trial.

### Statistical analysis

Inferential analyses: To examine quantitative feasibility measures, we will use Fisher’s exact tests when expected cell counts <5 and *t* tests to compare feasibility scores between the low and moderate dose groups. Significant differences between the two groups will indicate which yoga group is more feasible. We will also use logistic and Gaussian regression analyses to further compare feasibility scores between groups while adjusting for baseline participant characteristics.

We will use Fisher’s exact tests and ANOVAs to compare quantitative acceptability scores across control and yoga groups. Logistic and Gaussian regression analyses will be used to compare scores while adjusting for baseline participant characteristics. We expect participants in the control group to report similar levels of acceptability compared to those in the yoga groups, but participants in the yoga groups are expected to report greater improvements on outcomes than control participants.

Descriptive analyses: SPSS and *R* will be used to conduct descriptive statistical analyses, including graphical analysis (e.g., scatter plots, boxplots and histograms) and data summarization (e.g., means, medians, ranges, cross-tabulations) to identify data entry errors, outliers, and non-normal distributions. Standard errors and confidence intervals will be calculated using either parametric or non-parametric methodology, including the use of the bootstrap to estimate standard errors when parametric assumptions fail.

Data from the qualitative interviews will be transcribed and independently coded by the research team using NVivo. After coding is complete, researchers will meet to reach agreement on major themes of the interviews. Once the major themes have been determined, findings will be verified through member checking to determine accuracy of findings. Principal Investigator (PI) [name] and Co-I [name] have extensive training and experience in qualitative methods.

Psychometric analyses: We will evaluate scale reliabilities using Cronbach’s alpha coefficients based on baseline (T1) data. Scale inter-correlations will be estimated along with complete descriptive statistics on scale items.

Randomization check: We will also conduct an ANOVA to compare the experimental and control groups on outcome and demographic variables at baseline.

#### Missing data

Substantial missing data are anticipated in this study. Participants may refuse to participate or withdraw from the study at any time. In addition, daily and weekly logs may not be complete despite efforts by research staff to encourage completion. Missing data due to non-response on certain items within a scale will initially be handled by creating an average scale score for all participants who responded to at least 75% of items on that scale. We will evaluate whether missingness due to attrition is related to group membership and examine relations between missingness and any missing individual’s pretest scores on outcome variables. If missingness is found to satisfy the missing at random assumption, we will handle the missing data using multiple imputation. Multiple imputation will also be used to handle item-level missingness for final analyses of scales. In the event that the missing at random assumption is violated, we will model the missing data mechanism and conduct sensitivity analysis on model parameters. All analyses will retain all participants who were assigned to the intervention or control groups (i.e., intent to treat).

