At 6 weeks (midway through the intervention), participants will be asked to complete the IES-R and answer a 1-item Likert-based question related to whether they think the intervention is contributing to their symptoms for the IMC to review. Every 2 weeks of the intervention, participants will be asked to fill out the PHQ-9 via Qualtrics within 48 h. A research team member will monitor PHQ-9 completion daily (including weekend/holidays). Women with scores suggestive of clinical depression (>15) will be notified and advised to follow up with their primary care physician. If suicidal ideation is noted with a screen score of two or three on question 9 of the PHQ-9, the participant will be contacted within 24 h by a crisis-trained, clinical staff for further assessment of risk. Clinical providers trained by the MISS Foundation are well equipped to handle psychological crises, have a system currently used for their existing 3000 grieving families they help annually, and have staff available on weekends/holidays. If imminent suicidal risk is present, the staff will follow MISS Foundation emergency procedures to ensure participant safety, and the participant will be discontinued from the study. If there are no concerns for active suicidal risk after the phone assessment, the participant will be able to continue in the study if she desires. All participants will have the MISS Foundation provider’s phone number, and the research personnel can either email, call, text, or page the lead clinical provider to respond to psychiatric issues. Depending on the need of the participant, one of them will be able to talk to a clinician within 2 to 3 h.

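### The missing-data rule conditions the sensitivity analysis on a check that cannot separate missing at random from missing not at random, and two sections disagree on whether imputation is conditional

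*Protocol article*

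**What the plan says.** The Missing data section, under Statistical analysis, opens with "Substantial missing data are anticipated in this study". It then names two comparisons: "We will evaluate whether missingness due to attrition is related to group membership", and the team will "examine relations between missingness and any missing individual’s pretest scores on outcome variables". Two conditional steps follow. The first is "If missingness is found to satisfy the missing at random assumption, we will handle the missing data using multiple imputation". The second is "In the event that the missing at random assumption is violated, we will model the missing data mechanism and conduct sensitivity analysis on model parameters". The section gives no other basis for deciding which condition applies.

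The Data management section says "Multiple imputations will be used to conduct statistical analysis with missing data", with no condition attached. Its next sentence repeats the conditional trigger: "In the event that the missing at random assumption is violated, we will model the missing data mechanism".

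Two other places bear on the point. The Sample size section assumes 20% attrition, from 90 enrolled to 72 with 20-week data. The Adverse events section describes outcome data collected between baseline and week 12: "At 6 weeks (midway through the intervention), participants will be asked to complete the IES-R", and the PHQ-9 is collected every two weeks.

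**The concern.** MAR and missing not at random (MNAR) differ in whether, given what was observed, dropout still depends on values that were not observed. Arm and baseline score are both observed. Comparing dropout with them can give evidence against missing completely at random (MCAR), but it can neither establish MAR nor show that it fails. The text nevertheless speaks of MAR as something that can be found to hold, and it makes the sensitivity analysis wait for a finding that it does not.

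The case that matters is a woman who worsens after baseline and then stops reporting. The plan itself describes one such route: a participant judged at imminent suicidal risk after a follow-up call is taken out of the study. Baseline scores need not reveal that kind of deterioration. If it is more common in one arm, the IES-R comparison is biased, and under the stated rule it could be reported with no sensitivity analysis beside it. That comparison is meant to help choose between the two yoga doses and to inform a full-scale trial.

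**Working it through.** **The plan's own figures.** 90 × (1 − 0.20) = 72, or 24 per arm, leaving 90 − 72 = 18 dropouts, or 6 per arm if spread evenly. The retained number reproduces and is not in question.

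**The logic of the rule.**

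- *Dropout is associated with arm or baseline score.* This is what MAR allows and what imputation handles. If it is read as a violation, the sensitivity analysis is triggered although MAR may hold.
- *Dropout is not associated with either.* Dependence on the unseen later score is not excluded. If this is read as MAR satisfied, the sensitivity analysis is omitted although MAR may fail.
- *An association is not read as a violation either.* Then neither result of the two named comparisons can trigger the sensitivity analysis.

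**A simulation of the check.** The inputs from the plan are 90 women, 30 per arm and 20% dropout. The rest is assumed: standardised baseline and outcome with correlation 0.5, a true arm difference of 0, higher scores worse, logistic dropout with slope 1.0 or 1.5 per SD, and 4,000 runs. A run counts as flagged if dropout is related to baseline score (t test) or to arm (chi-square) at p < 0.05. That threshold is also an assumption, because the plan gives none. The MAR-based estimate is the baseline-adjusted difference, yoga arms together against control, among completers.

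| Dropout depends on | Runs flagged (slope 1.0 / 1.5) | Error in yoga − control, SD (1.0 / 1.5) |
|---|---|---|
| nothing (MCAR) | 10% / 10% | 0.00 / 0.00 |
| baseline score (MAR) | 93% / 99.7% | 0.00 / 0.00 |
| the outcome itself (MNAR) | 40% / 61% | about 0 / about 0 |
| the part of the outcome that baseline does not explain (MNAR) | 10% / 10% | 0.00 / 0.00 |
| the same part, in opposite directions in yoga and control (MNAR) | 10% / 10% | −0.30 / −0.39 |

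The 10% is the false-alarm rate of two tests at 5%: 1 − 0.95² = 0.0975. The check is flagged most often when MAR holds and the estimate is unbiased. It stays at its false-alarm rate in the one case where the arm difference is biased. MNAR that acts alike in all arms leaves the difference close to unbiased, so the concern for the comparison is MNAR that differs by arm.

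**Size on the IES-R scale.** Let imputed scores be too good by δ_y points in yoga dropouts and δ_c in control dropouts. With 20% imputed in each arm, the arm difference moves by 0.20 × (δ_y − δ_c). Assume δ_c = 0 and δ_y = 5 to 15:

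- 0.20 × 5 = 1.0 point; 1.0 / 15 = 0.07 SD
- 0.20 × 15 = 3.0 points; 3.0 / 15 = 0.20 SD

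The shifts and the SD of 15 are assumptions; the article gives none of them. If δ_c equals δ_y, the difference does not move. For scale, the standard error of a two-arm difference with 24 per arm is √(2/24) = 0.29 SD, and the plan targets d = 0.80.

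**The case against.** The strongest reply is that the plan already names the right tools, namely multiple imputation, modelling of the missingness mechanism, sensitivity analysis and retention of all randomised women, and that only the conditional wording is at fault. Several parts of this stand.

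- A reader might infer that the main method itself depends on the data. The documents do not support that without qualification, because Data management states multiple imputation with no condition. The two sections conflict and must be reconciled.
- A reader might infer that the sensitivity analysis will certainly run on the wrong trigger or never. The text does not say that an association counts as a violation, gives no threshold, and does not say that the two comparisons are the only evidence. Reasons for dropout are also compiled for the annual report. What the text supports is that the trigger may misfire in either direction.
- A reader might infer that the comparisons carry no information about the unseen scores. That is too strong. Baseline and outcome are likely to correlate, and in the simulation dropout driven by the outcome itself was flagged in 40% to 61% of runs against 10% under MCAR. But MAR was flagged more often still, so a flag does not tell the two apart.
- The expectation of substantial missing data is explained partly by incomplete daily and weekly logs, not by the IES-R alone. The figure stated for attrition is 20%.
- The largest simulated bias comes from one constructed pattern, and the largest shift computed on the IES-R scale (0.20 SD) is below one standard error (0.29 SD).

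It does not stand that this is detail left to a statistical analysis plan. The article states the decision rule, and a plan that followed it would inherit the fault. Nor does the unconditional sentence under Data management repair the trigger, because the sentence after it repeats the condition.

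**Conclusion.** The point holds for the rule as written. Comparing attrition with arm and baseline scores cannot decide between MAR and MNAR, so making the sensitivity analysis conditional on that decision may produce it when it is not needed and omit it when it is. The status of multiple imputation also differs between the two sections. The logical part rests on no numerical assumption.

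The size does. A movement of 1 to 3 IES-R points (0.07 to 0.20 SD) needs 20% dropout, a 5 to 15 point shift confined to yoga dropouts and an SD of 15, and only the dropout rate is in the article. It should not be read as an estimate of bias in this trial. The effect falls on the exploratory PTSD comparison, which the plan says is not fully powered. Nothing here shows an effect on the feasibility and acceptability benchmarks, which are the lead objectives. It is worth correcting because the correction is cheap, but it does not threaten the trial's main purpose.

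**What to change.** 1. Reconcile the two sections: state MAR as the assumption of the main analysis and use multiple imputation unconditionally, as Data management already says.
2. Put arm and baseline scores in the imputation model and, where feasible, the week-6 IES-R and the two-weekly PHQ-9 already collected for safety. Imputing separately within each arm is not required and could be unstable with about 24 completers per arm.
3. Keep the comparisons of missingness with arm and baseline scores as description only, and remove the wording about MAR being found to hold or violated.
4. Always report a pre-specified MNAR sensitivity analysis for the IES-R, whatever the comparisons show. One example is delta-adjusted imputation over a stated range, with the shift allowed to differ by arm.

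The cost is a change of wording and a few extra analysis runs. No new data are needed, and the 90 enrolled and 72 retained are unchanged.

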### Data monitoring

Due to the nature of this study, an IMC will be established and comprised of four committee members. Due to their combined expertise related to stillbirth care, biostatistics, NIH-funded studies, and yoga safety, they are qualified to review the patient safety data generated by this study.

#### Adverse events

An AE is any untoward medical occurrence in a subject during participation in the clinical study or with use of the experimental agent being studied. An adverse finding can include a sign, symptom, abnormal assessment (laboratory test value, vital signs, electrocardiogram finding, etc.) or any combination of these regardless of relationship to participation in the study. Adverse events that are non-serious will be provided to the IMC with summaries of the numbers and rates of AEs by group.

Expedited review will occur for all events meeting the FDA definition of serious adverse events (SAEs), i.e., any fatal event, immediately life-threatening event, and permanently or substantially disabling event. This also includes any event that a study investigator or the IMC judges to impose a significant hazard, contraindication, side effect, or precaution. For purposes of this study, all SAEs will be reported to the IMC regardless of any judgment of their relatedness to the study treatment.

The PI will record all reportable events with start dates occurring any time after informed consent is obtained until 7 (for non-serious AEs) or 30 days (for SAEs) after the last day of study participation. Each week, participants will report in their weekly logs the occurrence of AE/SAEs since the last week. If the participants are not completing their logs, they will be prompted via email by the research team to complete their logs. If there are two consecutive failed email attempts, the participants will be called. Events will be followed for outcome information until resolution or stabilization.

The research team will determine if the event is an AE or an SAE. If an SAE, the research team will complete a form to be provided to the IMC to meet and investigate the SAE until determined resolved or stable and its relation to the study (related or not related). Once recruitment begins, IMC will meet twice a year and will meet ad hoc when AE or an SAE occur. AE reports and annual summaries will not include individual identifiable private information about the human subjects. Each report will only include the identification code previously assigned.

At 6 weeks (midway through the intervention), participants will be asked to complete the IES-R and answer a 1-item Likert-based question related to whether they think the intervention is contributing to their symptoms for the IMC to review. Every 2 weeks of the intervention, participants will be asked to fill out the PHQ-9 via Qualtrics within 48 h. A research team member will monitor PHQ-9 completion daily (including weekend/holidays). Women with scores suggestive of clinical depression (>15) will be notified and advised to follow up with their primary care physician. If suicidal ideation is noted with a screen score of two or three on question 9 of the PHQ-9, the participant will be contacted within 24 h by a crisis-trained, clinical staff for further assessment of risk. Clinical providers trained by the MISS Foundation are well equipped to handle psychological crises, have a system currently used for their existing 3000 grieving families they help annually, and have staff available on weekends/holidays. If imminent suicidal risk is present, the staff will follow MISS Foundation emergency procedures to ensure participant safety, and the participant will be discontinued from the study. If there are no concerns for active suicidal risk after the phone assessment, the participant will be able to continue in the study if she desires. All participants will have the MISS Foundation provider’s phone number, and the research personnel can either email, call, text, or page the lead clinical provider to respond to psychiatric issues. Depending on the need of the participant, one of them will be able to talk to a clinician within 2 to 3 h.

If at any time during the study a participant should call a member of the research team emotionally distressed, not making clear sense, sounding intoxicated or impaired, or expressing thoughts of suicide or homicide, the research personnel will use a second phone line to contact the counselor, without losing verbal contact with the woman. At that point, the clinician will guide the interview to ascertain the acuity and/or potential for harm and will first determine if the caller is alone or has access to another adult capable of transportation. If determined that the woman is in need of emergent care, options for such care will be discussed with the caller and may include referral to the closest emergency room (ER), notification of emergency services for transportation to the nearest ER, and emergent counseling appointment coordinated by the MISS Foundation or their preferred provider. If the subject declines such a referral and the clinician remains concerned about the participant’s safety, emergency services in her area (determined during the consent process) will be notified of the clinical concern for safety.

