### Eligibility criteria

Inclusion and exclusion criteria for phase 1 (iterative design and interviews) are described in Table 1, and those for phase 2 are described in Table 2.

**Table 1 Tab1:** Phase 1 eligibility criteria

Inclusion
Iterative design
• Able to read/understand/speak English
• Women who experienced stillbirth within past 6 weeks to 24 months OR
• Women who have not experienced stillbirth but have given at least one live birth who regularly practice yoga (participate in yoga >60 min/week)
Interviews
• Able to read/understand/speak English
• Racial/ethnic minority women
• Women who experienced stillbirth within past 6 weeks to 24 months
• Not regularly practicing yoga (participating in yoga <60 min/week)
• Underactive (≤120 min/week moderate-intensity physical activity)
Exclusion
Iterative design
• Women who have experienced stillbirth that regularly practice yoga (i.e., ≥60 min/week)
• Pregnant women
• Unstable psychiatric condition (psychosis; suicidal ideation with plan)
Interviews
• Caucasian women
• Unstable psychiatric condition (psychosis; suicidal ideation with plan)

**Table 2 Tab2:** Phase 2 eligibility criteria

Inclusion
• Women who experienced stillbirth within past 6 weeks to 24 months
• Clinical levels posttraumatic stress symptoms (score of ≥33 on IES)
• ≥18 years of age
• Residing in the USA
• Able to read/understand/speak English
• Underactive (≤120 min/week moderate-intensity physical activity)
• Willing to be randomized
• Regular internet access via mobile phone, desktop/laptop computer, tablet, and etc.
• Answer “no” to all items on the PAR-Q (can participate safely)
Exclusion
• Unstable psychiatric condition (psychosis; suicidal ideation with plan)
• Pregnant at time of enrollment^a^
• Practicing yoga at least 60 min/week
• Unwilling to be randomized to a group
• Score of 20–27 of PHQ-9 (severe depression score)
• At risk for suicide based on follow-up phone assessment by [name] after positive screen (PHQ-9 score of 1, 2, or 3)

^a^Pregnant women will not be eligible for initial recruitment into the study. Women who become pregnant during the study will complete a PARmed-X for Pregnancy with their physician to identify any contraindications to yoga and will be able to continue participation

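### A PHQ-9 question 9 answer that rises from 0 at entry to 1 on study triggers no suicide risk assessment, although Table 2 treats a 1 as a positive screen

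*Protocol article*

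**What the plan says.** **Entry (Eligibility criteria, Table 2).** One exclusion reads "At risk for suicide based on follow-up phone assessment by" a named clinician "after positive screen (PHQ-9 score of 1, 2, or 3". A woman with any of these three scores is phoned, and she is excluded if the call finds her at risk.

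**On study (Adverse events).** The schedule is "Every 2 weeks of the intervention, participants will be asked to fill out the PHQ-9 via Qualtrics within 48 h". Two actions depend on the result:

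- Question 9: "If suicidal ideation is noted with a screen score of two or three on question 9 of the PHQ-9", crisis-trained staff contact her within 24 hours to assess risk. She is discontinued if the risk is imminent and may otherwise continue.
- Total score: "Women with scores suggestive of clinical depression (>15) will be notified and advised to follow up with their primary care physician".

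**Other provisions in the same section.** Staff have an optional route: "the research personnel can either email, call, text, or page the lead clinical provider to respond to psychiatric issues". Every participant holds the provider's phone number, and a distress-call procedure starts when a participant rings the team. Adverse events are reported weekly. They are defined broadly ("An adverse finding can include a sign, symptom, abnormal assessment") and followed up ("Events will be followed for outcome information until resolution or stabilization").

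**Outcome schedule (Outcome measures, Table 3).** The PHQ-9 is also completed at baseline, 12 weeks and 20 weeks.

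**The concern.** The same answer to the same question is handled in two ways. At entry a 1 is enough for a clinician to phone and judge suicide risk. On study a 1 starts nothing.

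The affected group is narrow. A woman who scored 1 to 3 at entry has already been phoned and cleared. A woman who answered 0 was not phoned under this criterion. If she later answers 1, she has moved into the range that Table 2 calls positive, and still no assessment follows from the score.

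The setting gives this weight. Participants enter with clinical levels of post-traumatic stress symptoms, and the Background names suicidal thoughts among the reactions seen in bereaved mothers. They are recruited nationally and take part online at home, so the two-weekly PHQ-9 is one of the few regular signals the team receives. The decision to discontinue for imminent risk also follows from the phone assessment, which a new 1 does not start.

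**Working it through.** The document gives no figure to reproduce here. The check is a comparison of the two rules, plus a ceiling on the workload of the fix.

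**1. What the Table 2 score is.** Table 2 does not name question 9. The Depression section gives total scores of 0 to 27, with mild symptoms starting at 5. A total of 1 to 3 lies below that cut-off and could not define a suicide screen. The values 1, 2 and 3 must be answers to question 9.

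**2. The two rules side by side.**

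| Question 9 answer | At entry (Table 2) | On study (Adverse events) |
|---|---|---|
| 0 | no call under this criterion | no call |
| 1 | phone risk assessment | no score-triggered action |
| 2 | phone risk assessment | contact within 24 h |
| 3 | phone risk assessment | contact within 24 h |

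The positive set is {1, 2, 3} at entry and {2, 3} on study. One of three positive answers loses its trigger.

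**3. Whether another provision closes the gap.**

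- Total above 15: leads to advice to see a primary care physician, not to a suicide risk assessment. A woman with a 1 on question 9 and a total of 15 or less does not get even that.
- Contacting the lead clinical provider: staff may do so, but nothing obliges them to at this answer.
- Provider's number and distress-call procedure: both need the woman to call.
- Weekly questions on mental health, counselling and adverse events (Procedures; Adverse events): these lead to recording, follow-up and committee reporting. No clinician call is tied to question 9.
- Six-week IES-R: reviewed by the monitoring committee. It is not a question 9 trigger.

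None ties a risk assessment to a new answer of 1.

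**4. Ceiling on calls under the fix.** The fix calls a woman when her answer is 1 and her previous answer was 0.

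- Two-weekly forms: 12 weeks / 2 weeks = 6.
- Adding the 20-week form: 6 + 1 = 7 if the sixth two-weekly form doubles as the 12-week form, or 8 if the two are separate.
- Each rise needs a 0 directly before it. Starting from 0 at entry, rises can fall only on every other form (1st, 3rd, 5th, 7th), so there are at most 4 per woman with either 7 or 8 forms.
- For 90 women: 4 × 90 = 360.

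This is a logical limit, reached only if every woman alternated between 0 and 1 throughout. It is not a forecast. The document gives no frequency of question 9 answers, so the expected number of calls cannot be derived.

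**The case against.** The strongest reply is that the two rules serve different decisions. Table 2 decides whom to keep out before randomization, where a wide net is usual. The on-study rule sends crisis-trained staff within 24 hours, and a higher threshold for an urgent contact is coherent. This stands in part: a deliberate choice cannot be excluded, and a reader who infers that the protocol contradicts itself goes further than the text allows. It does not explain why a new 1 should lead to no assessment at all, even a less urgent one.

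A second reply is that operating detail sits elsewhere. The Research ethics approval section mentions approved safety monitoring plans, Table 5 lists a manual of procedures, and the partner foundation has its own emergency procedures. Any of these might cover a 1, and that cannot be ruled out. The point nevertheless concerns a numeric threshold that the article states, with its deadline and the staff responsible, rather than detail left out of a condensed text.

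A third reply is that the practical gap is small. During the intervention a woman who moves from 0 to 1 is asked again within two weeks, and a 2 or 3 then brings the call. Staff check PHQ-9 completion daily, and the weekly log asks about mental health. This stands as a limit on size. It would be wrong to infer that nothing can happen at a score of 1, because discretionary and participant-initiated routes remain. It would also be wrong to extend the point to every woman who answers 1 on study, since those who were positive at entry had already been assessed.

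**Conclusion.** The point holds in a limited form. The on-study trigger leaves out one of the three answers that the trial's own entry screen treats as positive. The women affected are those who answered 0 at entry and newly answer 1. They receive no score-triggered risk assessment, and no other provision in the article ties one to that answer.

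This rests on reading the Table 2 score as question 9, which the Depression cut-offs support, and on the article's stated rule being the one in use. It does not establish that the difference is a mistake or that these women have no route to help. The number affected is unknown. The case for changing the rule is that the answer is already collected, form completion is already monitored daily and the clinical staff are already in place. The change is worth making for safety. It affects no endpoint, sample size or analysis.

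**What to change.** In Adverse events:

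- Keep the 24-hour contact for any question 9 answer of 2 or 3.
- Add a phone risk assessment by the same crisis-trained staff, not necessarily within 24 hours, for any answer of 1 that is higher than the woman's previous question 9 answer.
- State that this covers the two-weekly forms and the 12- and 20-week PHQ-9 in Table 3.
- State that a 1 repeating the previous answer needs no new call if the woman has already been phoned and cleared.

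Comparing with the previous answer also catches a woman who was phoned at entry, returned to 0 and rose again.

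In Table 2, write 'PHQ-9 question 9 score of 1, 2, or 3'. Do not narrow the entry screen to match the on-study rule.

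Cost: a sentence or two in Adverse events, two words in Table 2, a survey alert that compares each answer with the one before, and some extra calls by existing staff. Their number cannot be estimated from the document.
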